### Experimental procedures

Once screened and recruited, participants will be invited to their pseudo-randomly allocated experimental session [31]. They will come to the laboratory wearing comfortable, loose-fitting attire. Upon arrival, participants will be seated whilst they acclimatise to the ambient conditions of the laboratory (22–24 °C; 50% RH) before recording height and body mass (Model 874; Seca GmbH, Hamburg, Germany).

Following the pre-experimental checks, participants will lie down in the prone position on a hospital bed. Care will be taken to ensure that participants are as comfortable as possible by providing pillows as necessary to support the pelvic region and upper body, given the length of time (75 minutes) they will need to remain in this position. The addition of the pillows also serves to support the lumbar region by flattening the sacroiliac joint and reducing any pronounced lordosis of the spine while lying in a prone position.

First, structural, and functional imaging of the skin of the sacral skin using Optical Coherence Tomography (OCT) will be performed. This will be followed by sampling of skin sebum at the sacrum for subsequent biomarker analysis, using an established methodology involving a 2-minute application time and tweezer extraction to avoid cross-contamination [32]. The investigator will then place a custom-built thermal probe over the sacrum and load it with a weight (see below for details) to achieve pressure of 60 mmHg. The thermal probe consists of a water-perfused set of Peltier elements, which provide local temperature control for a 36-cm^2^ plate. An optic fibre is integrated in the plate, flush to its surface, which allows for the continuous monitoring of skin blood flow via Laser Doppler Flowmetry (LDF). The thermal probe is mounted on a frame with an integrated strain gauge to estimate the force applied to the stimulator. When applied to the skin, the integrated device allows for the manipulation of local skin temperature (range: 0°C to >50°C; variable temperature rates under PID control), applied pressure and the concurrent monitoring of blood flow.

To ensure consistent placement between sessions, probe placement will be marked with non-permanent ink. To minimize edge loading, the thermal probe is equipped with a 3D printed sleeve (thermoplastic polymer (Poly lactic acid)) and to ensure uniform pressure distribution across the mechanically loaded sacrum an interface pressure mapping device will be used (ForeSiteSS, XSensor, Canada). The pressure mapping device comprises a 2*32 sensing array with a spatial resolution of 12.7mm, operating between 5-256mmHg, with an accuracy of ± 5%.

Finally, participants will be asked to provide subjective ratings of thermal sensation, comfort, and acceptability, using Likert scales (detailed below). At this point, the standardised protocol to cause pressure-induced ischemia and post-occlusive hyperaemia will commence (Fig 2).

**Fig 2 pone.0303342.g002:**
[figure not shown]
Standardise pressure protocol delivered over the sacrum. The thermal probe will be used to deliver a standardised 60mmHg pressure protocol to evoke pronounced tissue ischaemia under 3 thermal conditions, i.e. a control skin temperature evoking no cooling (i.e. 38°C) and two cooling temperatures of 24°C and 16°C. During the protocol, a series of non-invasive measurements will be conducted [i.e. skin blood flow via LDF; inflammatory biomarker sampling from skin sebum; structural and functional imaging via Optical Coherence Tomography (OCT); perceptual assessment of subjective thermal sensation, comfort, and acceptance] at different time points (identified in the diagram by ↑).

The protocol consists of three phases; i) a 10-minute baseline stabilisation with minimal pressure (17.5 mmHg (2.3 kPa)), ii) 45-minute loading phase (60 mmHg/7.9 kPa [15)), and iii) a 20-minute minimal pressure phase (same as baseline). Skin blood flow will be measured continuously throughout the three phases of the protocol via Laser Doppler Flowmetry (Moor Instruments, moorVMS-LDF laser Doppler monitor, UK) with perceptual responses measured at predetermined intervals during the protocol (Fig 2). During the baseline phase in all conditions, the temperature probe will be set to 34 °C. On starting the loading phase, the thermal probe will be loaded with a 2 kg weight to elicit an equivalent pressure of 60mmHg (7.9 kPa) at the probe interface. The initial 5-mintues of the loading phase will serve as a further baseline measurement for the pressure protocol, to delineate the effects of 60mmHg loading alone on microvascular responses. To this end, once the load is applied to the sacrum, the probe temperature will remain at 34 °C. Following this, the temperature probe will be set to the target temperature for the specific testing session, either 38 °C (Δ13.7 °C/min), 24 °C (Δ11.3 °C/min), or 16 °C (Δ9.2 °C/min) and will be maintained at such temperature until the end of the session.

Upon completion of the loading phase, the thermal probe will be unloaded (Fig 2) whilst maintained in position over the sacrum, to allow skin tissue blood flow reperfusion (which will be continuously monitored by via LDF). The minimal loading phase (comparable to the initial 10-minute baseline phase) will last for 20 minutes, after which the thermal probe will be removed to allow for image acquisition via OCT and a final sampling of skin sebum over the sacrum.

The sections below provide a detailed description of each measurement undertaken during the protocol.

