## Measurements

### Skin blood flow

Continuous skin blood flow will be monitored via Laser Doppler Flowmetry at the sacrum.

LDF is a non-invasive technique that uses optical probes to measure blood flow velocity in the microvasculature. Typically, tissue thickness is sampled at 1mm implementing the Doppler principle whereby light from a monochromatic laser becomes scattered from moving red blood cells, allowing it to be applied to a wide range of anatomical locations [33]. Given its relative low cost and ease of use, LDF is validated [34] and has been widely used to assess changes in blood flow velocity (as an index of changes in flow) over bony prominences, such as the sacrum [6, 13–15, 35].

The optical probe is integrated within the custom-built temperature probe, allowing concurrent manipulation of skin temperature whilst monitoring real-time changes in skin blood flow, during loaded and minimal loaded states. Blood flow during the loading phase will be analysed via spectral analysis of wavelet frequency to investigate temperature-modulated regulatory mechanisms during loading (i.e. changes in 0.1 Hz, 0.04 Hz, and 0.01 Hz frequencies will be associated with myogenic activity of vascular smooth muscles, neurogenic activity of the vessel wall, and vascular endothelium related metabolic activity, respectively) [11]. Blood flow during the minimal loading phase will be used to calculate the baseline skin blood flow (taken as the mean average during the final 3-minutes of the 10-mintue baseline period). The average baseline will then be used for normalisation of peak hyperaemia [(peak hyperaemia—average baseline skin blood flow)/average baseline skin blood flow)*100)] to investigate its modulation via cooling. Changes in peak hyperaemia represent a robust and repeatable microvascular response [36], which is directly implicated in the pathophysiology of PUs [36]. Secondary perfusion parameters will include the time to peak hyperaemic response and the perfusion area between the skin blood flow response curve and the mean baseline skin blood flow after unloading and during the reperfusion phase. In the measurement of peak hyperaemia skin blood flow will be collected continuously (40 Hz sampling rate) and averaged every 1-minute for the analysis of the temporal dynamics of cooling induced changes in skin blood flow under loading.

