### Statistical analyses

Data will be assessed for normality of distribution (Kolmogorov—Smirnov test), and then analysed for the independent and interactive effects of pressure stimuli’s temperature (i.e. 3 levels: 38, 24, 16 °C), and of participant group (i.e. 3 levels: young, older, SCI) on within- and between-subject mean differences in peak hyperaemia (N = 35 with 95% Confidence Intervals). This will be conducted using a 2-way mixed model ANOVA or Friedman, depending on the data distribution (parametric or non-parametric, respectively). Post-hoc analyses will be performed between pressure stimuli’s temperatures and participant groups based on the presence of main effects and using Tukey’s test. The use of regression models will evaluate the relationship between absolute cooling temperatures and peak hyperaemia during pressure stimuli. This approach is designed to identify “physiological thresholds” for the protective effects of cooling under mechanical loading. Mean thresholds will subsequently be determined and their inter-individual variability across the cohort. For the perceptual data, thermal discomfort will identify “Uncomfortable” on the Likert Scale as the threshold onset of discomfort. Regression analyses will be used to interrogate the relationship between pressure stimuli’s cooling temperature and local discomfort, for each participant. This approach will also enable the assessment of “perceptual cooling thresholds” for cold-induced discomfort at two absolute cold temperatures (i.e. 24 and 16 °C), and their individual variability. Physiological and perceptual thresholds will be combined to produce common cooling parameters that will accommodate different cooling characteristics. Regarding the secondary experimental outcomes, these will be within- and between-subject changes in biomarkers’ expression, skin structural and biophysical properties (i.e. imaging parameters and skin friction), and subjective thermal perceptions, as a function of pressure stimuli temperature (i.e. 3 levels: 38, 24, 16°C), time (i.e. varying levels depending on variables’ sampling rate), and of participant group (i.e. 3 levels: young, older, SCI). Data will be first assessed for normality of distribution (Kolmogorov—Smirnov test), and then analysed for the independent and interactive effects of pressure and stimuli temperature, time, and participant group by means of a 3- way mixed model ANOVA (or Friedman). Post-hoc analyses will be performed between pressure stimuli temperatures, time, and participant groups based the presence of main effects and using Tukey’s test. Group-related co-variables associated with sex, skin tone, and clinical status (applicable to SCI participants only, e.g. rehabilitation status) will be considered in all analyses to interpret the proportion of variance unexplained by the main effects (i.e. temperature, time, and group) and their interactions.

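### The loaded 34 °C baseline recorded in every session has no role in the primary analysis; adjusting for it could sharpen the temperature contrasts at almost no cost

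*Protocol article*

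**What the plan says.** The text under Fig 2 in the protocol article sets three phases: 10 minutes at minimal pressure, 45 minutes of loading and 20 minutes at minimal pressure again. For loading, "the thermal probe will be loaded with a 2 kg weight to elicit an equivalent pressure of 60mmHg (7.9 kPa) at the probe interface". The probe stays at 34 °C for the first 5 loaded minutes in all three sessions, and only then moves to 38, 24 or 16 °C. The article gives those 5 minutes a purpose: the segment "will serve as a further baseline measurement for the pressure protocol, to delineate the effects of 60mmHg loading alone on microvascular responses". Blood flow is recorded continuously, so the value exists for every session.

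The Skin blood flow section defines baseline as the mean over the last 3 minutes of the unloaded 10-minute period, and continues: "The average baseline will then be used for normalisation of peak hyperaemia". Of the loaded period it says: "Blood flow during the loading phase will be analysed via spectral analysis of wavelet frequency". It also plans 1-minute averages for the time course under load.

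The Statistical analyses section tests temperature by group on peak hyperaemia, by a two-way mixed ANOVA or Friedman. The covariates that it names are "Group-related co-variables associated with sex, skin tone, and clinical status". The Participants section adds recorded confounders for the SCI group. Neither section gives the loaded 34 °C segment a place in the primary outcome or model.

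**The concern.** The weight standardises the load, but not how far flow falls under the optical fibre. The Limitations section accepts that a single probe may bring high variability from skin morphology and anatomy. If the flow response to load differs between a participant's sessions, and peak hyperaemia follows it, that difference enters the temperature contrasts as noise. The 34 °C segment measures the initial flow response in the same session, before the intervention, so the temperature setting cannot have affected it. Flow later in loading lacks this property. The article creates this second baseline for a declared purpose, but its primary analysis uses only the first. At stake is the width of the confidence intervals for 38, 24 and 16 °C.

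**Working it through.** **1. The stated load reproduces.** Inputs are the 2 kg weight, the plate ("which provide local temperature control for a 36-cm^2^ plate") and the 17.5 mmHg tare. Pressure = mass × g / area = 2 × 9.81 / 0.0036 m² = 5.45 kPa = 40.9 mmHg. Adding the tare gives 40.9 + 17.5 = 58.4 mmHg, which is 2.7% below 60 and within the pressure map's stated accuracy of 5% either way. This assumes that the tare stays in place during loading. The load is not in dispute.

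**2. Effect of the covariate on precision.** Let r be the within-participant, between-session correlation of 34 °C loaded flow with peak hyperaemia. The article does not give r, so a range is assumed. Residual variance is multiplied by 1 − r², the standard error by √(1 − r²), and 35 per group is then worth 35 / (1 − r²).

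| assumed r | variance × | SE × | 35 per group worth about |
|---|---|---|---|
| 0 | 1.00 | 1.00 | 35 |
| 0.2 | 0.96 | 0.98 | 36 |
| 0.3 | 0.91 | 0.95 | 38 |
| 0.5 | 0.75 | 0.87 | 47 |
| 0.6 | 0.64 | 0.80 | 55 |
| 0.7 | 0.51 | 0.71 | 69 |

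**3. Simulation check.** The setting was 3 × 35 participants, 3 sessions, 2,000 runs, and a true difference between 38 and 16 °C of 0.80 residual SD. The estimate was about 0.80 with and without adjustment. The unadjusted SE was 0.138, which agrees with √(2/105). With adjustment it fell to 0.132, 0.120 and 0.099 at r = 0.3, 0.5 and 0.7. The correlation is built into the simulation, so this confirms the formula and the absence of bias. It does not show what r is.

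**4. Form of the covariate.** Loaded flow as a percentage of baseline is the obvious choice, but the outcome, (peak − baseline) / baseline, has the same denominator. If loaded flow and peak are independent, each with an assumed coefficient of variation (CV) of 30%, the correlation induced by a baseline CV of v is about v² / (0.30² + v²):

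- v = 15%: 0.0225 / 0.1125 = 0.20
- v = 25%: 0.0625 / 0.1525 = 0.41
- v = 35%: 0.1225 / 0.2125 = 0.58

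Simulation gave 0.20, 0.40 and 0.55. This induced correlation is positive. Deeper ischaemia followed by a larger peak would give a negative one, so the two can cancel. In a simulation with 25% baseline variability, the ratio covariate had a within-participant r of about 0.04 and gave no gain. It never biased the temperature effect and raised its SE by at most about 1%. Log loaded flow and log baseline should therefore enter as separate terms.

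**The case against.** The strongest objection is about scope. Exact windows and further covariates often belong in an analysis plan that is not shown, and nothing here is a direct contradiction. That stands in part, and it is why the point is modest. Still, the article itself fixes the normalisation and names covariates, and leaves its own declared second baseline without a role.

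The article also has controls: ink marking of probe position, a strain gauge, and a pressure map "operating between 5-256mmHg, with an accuracy of ± 5"%. It cites evidence that single-site forearm measurement is reliable. These may reduce between-session variation and so make r small. They check position, force and pressure, however, and none measures the fall in flow.

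Three stronger readings are tempting, and the documents do not support them.

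- **Biased temperature contrasts.** A reader might infer this, but the Overview describes a randomised cross-over and Experimental procedures a pseudo-random allocation of sessions. Differences in occlusion between sessions are then noise.
- **Group differences in occlusion posing as a different response to cooling.** That response is the group-by-temperature interaction. An additive group offset is present in all three sessions and cancels. In a simulation with an assumed slope of 0.5 and shifts of 0.5 and 1 SD, the group main contrast moved to 0.25 and 0.51 (expected 0.5 × 0.5 = 0.25 and 0.5 × 1 = 0.50). The interaction stayed at 0.00, with 5% to 6% rejection. A small leak arises only if occlusion acts multiplicatively, which the article does not establish. The main effect of group can move, but unequal flow at equal load may be part of what ageing and SCI do, which is what the second aim asks about.
- **Diluted spectral outcomes.** The 34 °C segment is 5/45 = 11% of the loading phase, and the stated ramps take 4/13.7 = 0.29, 10/11.3 = 0.88 and 18/9.2 = 1.96 minutes. Dilution would require one pooled 45-minute average, which the article does not state. Since it calls the segment a baseline, using it as a reference is the natural reading.

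**Conclusion.** The point holds as one of efficiency. A pre-intervention value is recorded in every session for a declared purpose, and the primary analysis as described does not use it. The temperature contrasts remain valid. The possible gain is a standard error lower by about 5% at r = 0.3 and 20% at r = 0.6, and nothing if r is near zero. All of these values of r are assumptions. Five minutes at one site indexes the initial flow response to load, not the whole 45-minute ischaemic exposure, which is a further reason not to count on the upper end. No conclusion about bias in the group-by-temperature effect or about dilution of the spectra follows.

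**What to change.** In the primary mixed model, pre-specify as a covariate the within-participant deviation of log mean flow over the first 5 loaded minutes at 34 °C. Enter log unloaded baseline as a separate term, centred in the same way. The coefficient on loaded flow then does not rest on a shared denominator. Deviations sum to zero within a participant, so the group comparison stays unadjusted. The Friedman alternative cannot take a covariate, so this applies to the mixed-model analysis.

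Describe participant-mean loaded flow by group. Report any group result adjusted for it as a sensitivity analysis beside the unadjusted one.

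As a clarification only, state which minutes of the loading phase the spectral comparison between temperatures uses, and whether the 34 °C and ramp minutes are left out. As a reference for the slowest band the segment is weak: 300 s × 0.01 Hz = 3 cycles.

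The cost is analysis wording, since the signal is already recorded at 40 Hz. The downside is one or two extra covariates and possibly no gain. Recruitment began in January 2024, so the rule should be fixed before outcome data are examined.

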## Measurements

### Skin blood flow

Continuous skin blood flow will be monitored via Laser Doppler Flowmetry at the sacrum.

LDF is a non-invasive technique that uses optical probes to measure blood flow velocity in the microvasculature. Typically, tissue thickness is sampled at 1mm implementing the Doppler principle whereby light from a monochromatic laser becomes scattered from moving red blood cells, allowing it to be applied to a wide range of anatomical locations [33]. Given its relative low cost and ease of use, LDF is validated [34] and has been widely used to assess changes in blood flow velocity (as an index of changes in flow) over bony prominences, such as the sacrum [6, 13–15, 35].

The optical probe is integrated within the custom-built temperature probe, allowing concurrent manipulation of skin temperature whilst monitoring real-time changes in skin blood flow, during loaded and minimal loaded states. Blood flow during the loading phase will be analysed via spectral analysis of wavelet frequency to investigate temperature-modulated regulatory mechanisms during loading (i.e. changes in 0.1 Hz, 0.04 Hz, and 0.01 Hz frequencies will be associated with myogenic activity of vascular smooth muscles, neurogenic activity of the vessel wall, and vascular endothelium related metabolic activity, respectively) [11]. Blood flow during the minimal loading phase will be used to calculate the baseline skin blood flow (taken as the mean average during the final 3-minutes of the 10-mintue baseline period). The average baseline will then be used for normalisation of peak hyperaemia [(peak hyperaemia—average baseline skin blood flow)/average baseline skin blood flow)*100)] to investigate its modulation via cooling. Changes in peak hyperaemia represent a robust and repeatable microvascular response [36], which is directly implicated in the pathophysiology of PUs [36]. Secondary perfusion parameters will include the time to peak hyperaemic response and the perfusion area between the skin blood flow response curve and the mean baseline skin blood flow after unloading and during the reperfusion phase. In the measurement of peak hyperaemia skin blood flow will be collected continuously (40 Hz sampling rate) and averaged every 1-minute for the analysis of the temporal dynamics of cooling induced changes in skin blood flow under loading.

### Biomarkers

A preselected panel of pro- (IL-1α, IL-1β, TNFα, IL-6, IL-8, IFNγ) and anti-inflammatory biomarkers (IL-1RA) will be extracted from skin sebum. Biomarker collection and extraction techniques via application of Sebutape have been optimised in our laboratory [37], to ensure both low abundance and high abundance proteins can be quantified. In brief, Sebutape will be applied to the sacrum for 2-minutes before the samples are extracted using tweezers and a gloved hand to avoid cross contamination. Stored samples will be coded and stored at– 80 °C prior to analysis using standard ELISA plates for targeted proteins. The extraction of skin inflammatory biomarkers will use chemical and mechanical stimuli to for maximal extraction efficiency. Chemical extraction will involve 0.85 mL of extraction buffer, which consists of PBS + 0.1% Dodecyl maltoside. The tapes will then be shaken with the buffer for 1 hour followed by 5 minutes of sonication. A 0.35 mL aliquot will then be used for total protein analysis. The remaining 0.5 mL will be centrifuged for 10 minutes at a speed of 15 000g at 4°C. The supernatants will be discarded and the remaining solution with the pellet briefly vortexed and used for the immunoassay analysis, as prescribed by the manufacturer using MSD U-Plex kits (MesoScale Diagnostics).

### Skin imaging

Skin imaging via Optical Coherence Tomography using VivoSight^®^ device with dynamic OCT processing software (Michelson Diagnostics Ltd., Maidstone, Kent, UK) with a Class 1M (EN 60825–1) laser source of near-infrared wavelength (1305 nm). A total of 120 images with 50 μm spacing will be acquired as a 6 × 6 × 2 mm^3^ (width × length × depth) stack. This technique is non-inferior to punch biopsy for skin characterization [38] and will allow to non-invasively characterise the skin’s epidermal (i.e. thickness, stratum corneum hydration, collagen density) and blood perfusion properties (i.e. vascular plexus density and diameter) prior to and following the thermomechanical manipulations. This evaluation will also be relevant to model group differences in baseline skin anatomy and biophysics that may underlie the differential effects of cooling with ageing and SCI. The OCT probe will be placed gently on the skin, maintaining a static position during acquisition. Spacers at the probe interface will be used to optimise the focal point of the epidermis during scanning.

